### Interventions

After the screening visit and recording of informed consent, patients will be randomised into two treatment arms: “Step-up” and “Step-down”. Patients in the Step-up arm will be treated according to a conventional strategy based on treatment escalation and driven by the treat-to-target strategy. Patients in the Step-down arm will be treated with an early, combined, aggressive therapy for 6 months.

In the Step-up arm, less severe patients will receive IACI in all affected joints without systemic therapies. If the juvenile arthritis disease activity score-10 (JADAS10) state of minimal disease activity (MiDA) after 3 months or the JADAS10 inactive disease (ID) state at 6 months are not reached, treatment with MTX will be started preferably subcutaneously in a single weekly dose of 15 mg/m2 (max 20 mg) and IACI can be repeated. Then, if the states of JADAS MiDA after 3 months or JADAS ID at 6 months are not reached, treatment with an anti-TNF agent in a single weekly dose of 0.8 mg/kg (max 50 mg) subcutaneously will be started. More severe patients in Step-up arm will receive IACI(s) and MTX as a first step and then escalate therapy with the same pathway, adding an anti-TNF treatment as a second step and switching to a different biologic medication as a third step (Fig. 1).

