### Endpoints

The effectiveness of the two therapeutic strategies will be compared by assessing the frequency of clinical remission (CR) at 12 months [21]. CR is defined as the persistence of the JADAS10 state of ID for at least 6 months. Patients will be considered to be in ID from the day of the first visit with JADAS10 ID until the day before the first subsequent visit in which the patient is found to have lost the state of JADAS10 ID. Then, a number of secondary endpoints will be assessed in order to better understand the efficacy of the two treatment strategies (Table 3). The rate of patients achieving the JADAS-defined and the ACR-defined state of ID, the time to achieve ID and clinical remission, the time spent in inactive disease, the cumulative level of disease activity and the rate of uveitis will be compared between the two arms.

**Table 3 Tab3:** STARS trial endpoints

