**Primary endpoint**	
Clinical remission on or off medication at 12 months.	
The effectiveness of the two therapeutic strategies will be compared by assessing the frequency of clinical remission (CR) at 12 months. CR is defined as the persistence of the JADAS state of ID for at least 6 months	

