The cumulative time on therapy will be calculated as the time difference (in days) between the date of the visit on which the patient will start a systemic medication (synthetic or biologic DMARDs or steroids) and the date on which he/she will be observed to no longer be in treatment with a systemic medication or completed the study. We assume that if a patient does not receive medications at 2 consecutive visits, the patient had not received medications everyday between these visits. Patients initiating a systemic treatment at the final visit of the study will contribute a single day of time in therapy. The mean percentage of time spent on therapy per patient will be recorded and compared between the 2 arms.	
Rate of flares	
The rate of patients who develop flare, defined as the recurrence of active disease after attaining inactive disease at last visit according to JADAS or JIA ACR definition, and the number of flares and the time to flare per patient will be recorded and compared. Notably, all patients prescribed intra-articular injections, synthetic or biologic DMARDs or systemic steroids will be considered as flare independently from JADAS or ACR criteria.	
Rate of uveitis onset	
The rate of patients who develop uveitis according to the Standardized Uveitis Nomenclature (SUN) will be recorded and compared between the 2 arms. The rate of patients requiring systemic medications for treatment of uveitis will be also recorded and compared between the 2 arms. However, these patients will be excluded from the study and followed for safety only.	

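### The treatment clause in the flare definition has no prior-remission, new-treatment or timing limit, so as written every child in both arms is a flare at baseline

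*Protocol article*

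**What the plan says.** Table 3 of the protocol article, under Rate of flares, gives two sentences on what a flare is. The first is a disease criterion: "defined as the recurrence of active disease after attaining inactive disease at last visit according to JADAS or JIA ACR definition". The second is a treatment criterion: "all patients prescribed intra-articular injections, synthetic or biologic DMARDs or systemic steroids will be considered as flare independently from JADAS or ACR criteria". Three quantities are to be compared between arms: the proportion of children with a flare, the number of flares and the time to flare. The Analysis plan assigns time to flare to Kaplan-Meier curves and the log-rank test.

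The same table, under time spent in inactive disease, starts the clock at the first visit in ID and stops it when the disease flares, pointing forward to the flare definition. It also assumes that a child in ID at two consecutive visits was in ID on every day between them.

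The primary endpoint is defined without reference to treatment. Under Endpoints, "CR is defined as the persistence of the JADAS10 state of ID for at least 6 months", and a period of ID runs "until the day before the first subsequent visit in which the patient is found to have lost the state of JADAS10 ID". Table 3 describes it as "Clinical remission on or off medication at 12 months".

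**The concern.** The second sentence does not carry over the condition in the first that ID must have been attained. It also does not say that the treatment must be new or must come after randomisation. In this trial all of these matter, because the listed treatments are the interventions themselves: they start at baseline, are stepped up under the protocol and in some children continue through ID. A programmer who follows the sentence would count assigned treatment as disease recurrence. The flare comparisons would then reflect the treatment rules of the two arms at least as much as the return of arthritis.

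**Working it through.** **The plan's own figure.** No flare rate is stated, so there is none to reproduce. The sample size concerns the primary endpoint and reproduces. With 0.45 versus 0.25, two-sided alpha 0.05 (sidedness assumed) and power 0.80, n = [1.96·√(2·0.35·0.65) + 0.842·√(0.45·0.55 + 0.25·0.75)]² / 0.20² ≈ 88.1. The continuity correction raises this to 98, and 98/0.90 gives 109 per group, as stated. The flare definition does not enter it.

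**Reading 1: as written.** First treatments from Interventions:

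| Arm | Less severe | More severe |
|---|---|---|
| Step-up | injections | injections + methotrexate |
| Step-down | methotrexate + injections | methotrexate + etanercept |

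Each cell contains a listed treatment. The flare rate is 100% versus 100%, time to flare is zero for everyone, and the endpoint cannot separate the arms.

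**Reading 2: post-baseline prescriptions only.** Step-up children who miss minimal disease activity (MiDA) at 3 months, or ID at 6 months, start methotrexate or, at the next step, an anti-TNF agent ("if the states of JADAS MiDA after 3 months or JADAS ID at 6 months are not reached"). They count as flares even if never in ID.
- Month 3: the Step-up trigger is missing MiDA; the Fig. 1 legend also brings in a 50% JADAS improvement. The Step-down trigger is worsening from baseline. Two children with the same modest improvement can therefore be classified differently by arm.
- Month 6: Step-down children not in ID also change treatment, so both arms can generate such flares.
- After month 6: more severe Step-down children in ID continue methotrexate. If continued prescriptions count, they are flares too.

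**Illustration of what Reading 2 could do.** All flare rates here are assumptions.
- Take 260/2 × 0.90 = 117 children per arm and an equal true post-ID flare rate of 20%. Add never-ID children counted by the clause: 30% of Step-up and 10% of Step-down. The counted rates are 50% and 30%.
- Chance of a significant difference = Φ{[0.20 − 1.96·√(2·0.40·0.60/117)] / √((0.25 + 0.21)/117)} = Φ{(0.200 − 0.1255)/0.0627} = Φ(1.19) ≈ 0.88.
- Over true rates of 10% to 30%, and extra shares from 10% versus 0% up to 50% versus 25%, the chance runs from about 36% to 99%.
- With equal extra shares of 30% it stays at about 5%.

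The result depends on the difference in extra shares, which the documents do not give.

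**Time in ID.** Take a hypothetical child in ID at months 6, 9 and 12 and injected at month 8. The consecutive-visit rule gives 12 − 6 = 6 months in ID. The stop-at-flare rule gives 8 − 6 = 2 months, or 2 + 3 = 5 if ID is counted again from month 9. The article does not say which applies.

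**Overlap with the primary endpoint.** In oligoarthritis (ID cutoff 1.4), one active joint with every other item at 0 scores 1.0 and is still ID; adding 0.5 on one global scale gives 1.5 and ID is lost. In polyarthritis (cutoff 2.7), one active joint plus 0.5 on each global scale scores 2.0 and is still ID. If such a child is injected, the flare rule records a flare while the primary ID period continues.

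**The case against.** The best defence is context. The treatment sentence follows one that requires prior ID, and its reference to JADAS and ACR criteria may be meant to replace only the test for recurrence. The authors probably intended new treatment after ID, since a reading in which everyone flares at baseline empties time to flare of meaning. The article also summarises a fuller protocol that may carry the qualifier. The likely intent is granted. The published sentence still covers all patients and sets the criteria aside, so it is a stated rule that misfires rather than a detail left out. The time-in-ID conflict survives even under the intended reading.

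Three stronger conclusions are tempting, and the documents do not support them.
- A reader might infer a bias against Step-up. Only the month-3 trigger clearly differs; Step-down children not in ID at month 6 also change treatment, and continued methotrexate in Step-down may count.
- A reader might infer that escalation before first ID distorts time in ID. It cannot, because that clock starts at the first visit in ID.
- A reader might infer that the primary endpoint is faulty because a child can be both a flare and a remission. The overlap within one ID period is narrow, as the scores show, and no frequency is available. A child escalated at month 3 and then in ID from month 6 to month 12 is a legitimate success in a comparison of strategies that allows remission on medication.

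**Conclusion.** The flare definition is wrong as written. Followed literally, it gives 100% flares in both arms. Restricted to post-baseline prescriptions, it still counts children who were never in ID, under month-3 triggers that differ by arm. The flare rate, number of flares and time to flare are affected, as is the end date of time in ID for children treated between two ID visits. The size and net direction of any imbalance cannot be determined; the 36% to 99% range rests on assumed unequal shares and falls to about 5% when the shares are equal. The sample size and the primary test do not depend on this definition. This is a defect in secondary endpoints with a simple remedy.

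**What to change.** Reword the treatment clause so that it applies only to a new, re-started or intensified treatment for arthritis prescribed after the child has attained ID, with the flare dated at the prescription. State that baseline treatment, planned continuation (for example methotrexate continued in ID) and escalation before first ID do not count. Use this date consistently for flare rate, number of flares, time to flare and the end of time in ID, and say that it overrides the consecutive-visit assumption.

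Leave the primary endpoint definition unchanged. Ending the primary ID period at a prescription would redefine it after 113 children have been recruited and make it depend on prescribing decisions in a single-blinded trial. A supportive sensitivity analysis may treat such a prescription as ending the ID period.

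The cost is minor wording and a programming rule, settled before flare data are analysed. One practical condition remains: the article says that medication history is taken at each visit but not that the indication is recorded. The sponsor should confirm that treatment for arthritis can be told apart from other use.

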### Treatment adherence

Compliance will be monitored by study personnel at each study visit using diary cards and verbal information from the parent and/or subject. Reasons for missed doses must be recorded in the subject’s source documents and CRF.

Subjects provided with pre-filled syringes of investigational product will be instructed to return the empty packages and unused prefilled syringes in order to review drug accountability and subject compliance.

If more than four consecutive doses are missed due to adverse events (AEs), infections or surgeries, or if more than 2 consecutive doses are missed due to reasons other than AEs, infections or surgery, the Study Coordinating Centre must be consulted in order to determine whether the subject should continue taking investigational product.

### Sample size

Sample size calculations were extrapolated from a recent study of early aggressive therapy on JIA patients [11]. Using the sample size calculation for superiority trials with a delta of at least 20% (being the expected proportion of favourable outcome in the first arm p_1_ = 0.45 and in the second arm p_2_ = 0.25) and considering a drop out rate of 10%, a sample size of 109 patients in each group for a total of 218 patients will be required. Since an interim analysis is planned at enrolment of half of the sample, the total sample size was increased to 260 subjects. The trial will have 0.8 power for comparisons of the treatment arms, 0.05 type I error.

### Trial registration

The Trial is registered on the ClinicalTrials.gov registry (NCT03728478) on October 31st, 2018 and EU Clinical Trials Register on May 14th, 2018, Eudract Number 2018–001931-27.

## Discussion

This innovative trial compares the effectiveness of a conventional therapeutic regimen, based on treatment escalation and driven by the treat-to-target approach with that of an early aggressive combined intervention, including the first-line treatment with an anti-TNF agent in polyarthritis and more severe oligoarthritis. We chose to adopt a very robust primary endpoint by comparing in the two arms the frequency of patients who will achieve the end of the study in clinical remission, i.e., maintaining the status of inactive disease for at least 6 months. Therefore, if the trial will show a superiority of the more aggressive arm, we will provide important evidence supporting the theory of the existence for JIA patients of a window of opportunity, an early phase of the disease where treatment can possibly alter significantly the evolution of the disease. Furthermore, the comparison with an historical cohort of JIA children with the same disease features will allow us to demonstrate the effectiveness of two treatment strategies, both based on tight patient monitoring and treatment adaptation according to standardized disease activity measurement.

We acknowledge that the STARS trial has several potential limitations. One is the choice, for sake of uniformity, of etanercept as a first-line biologic medication in both arms. Etanercept is still the most widely adopted choice for non-systemic JIA and it is the biologic drug for which we have the longest experience on the field. However, we acknowledge that other drugs could also be the optimal choice in this population at higher risk for uveitis. Children requiring systemic medications due to uveitis will discontinue the trial and the comparison of the rate of uveitis between the two arms will be a secondary endpoint of the study.

### Trial status

This summary is based on version 3.0 of the study protocol, dated 15th November 2021. At the time of submission this trial is open in 22 hospital sites in Italy and has recruited 113 participants (Fig. 3), 57 in the less severe group, 56 in the more severe group. Fifty-seven children were randomised in the Step-up arm, 56 were randomised in Step-down arm. In the whole sample, the number of subjects lost at follow-up was 2. In general, recruitment has revealed to be more difficult than expected. This was mainly due to the COVID19 pandemics and to delays in the activation of secondary centres, as well as to the issue of randomization being an important barrier to enrolment. Indeed, subjects in the trial are children with very recent onset JIA and their families are at the beginning of the journey with this disease: even after a detailed description of the risk/benefit ratio in both arms, accepting that the first-line treatment is decided by a machine was a tough choice.

**Fig. 3 Fig3:**
[figure not shown]
Trial enrolment progression. In February 2021 most participating Italian centres obtained local IRB approval and we started monthly virtual Town Hall Meetings

## Data Availability

The datasets generated and/or analysed during the current study are available in the PRINTO repository (www.printo.it). The datasets used and analysed during the current study are available from the corresponding author on reasonable request.

## Abbreviations

AE: Adverse Event
CR: Clinical Remission
CRF: Case Report Form
DMARD: Disease Modifying Antirheumatic Drugs
ESR: Erythrocyte Sedimentation Rate
IACI: Intra-articular Corticosteroid Joint Injections
ID: Inactive Disease
JADAS10: Juvenile Arthritis Disease Activity Score-10
JIA: Juvenile Idiopathic Arthritis
MiDA: Minimal Disease Activity
MTX: Methotrexate
NSAID: Non-Steroidal Anti-Inflammatory Drugs
VAS: Visual Analogue Scale
